## Abstract

**Background:**

A timely differential diagnostic is essential to identify the etiology of central nervous system (CNS) infections in children, in order to facilitate targeted treatment, manage patients, and improve clinical outcome.

**Objective:**

The Pediatric Infection-Point-of-Care (PI-POC) trial is investigating novel methods to improve and strengthen the differential diagnostics of suspected childhood CNS infections in low-income health systems such as those in Southwestern Uganda. This will be achieved by evaluating (1) a novel DNA-based diagnostic assay for CNS infections, (2) a commercially available multiplex PCR-based meningitis/encephalitis (ME) panel for clinical use in a facility-limited laboratory setting, (3) proteomics profiling of blood from children with severe CNS infection as compared to outpatient controls with fever yet not severely ill, and (4) Myxovirus resistance protein A (MxA) as a biomarker in blood for viral CNS infection. Further changes in the etiology of childhood CNS infections after the introduction of the pneumococcal conjugate vaccine against *Streptococcus pneumoniae* will be investigated. In addition, the carriage and invasive rate of *Neisseria meningitidis* will be recorded and serotyped, and the expression of its major virulence factor (polysaccharide capsule) will be investigated.

**Methods:**

The PI-POC trial is a prospective observational study of children including newborns up to 12 years of age with clinical features of CNS infection, and age-/sex-matched outpatient controls with fever yet not severely ill. Participants are recruited at 2 Pediatric clinics in Mbarara, Uganda. Cerebrospinal fluid (for cases only), blood, and nasopharyngeal (NP) swabs (for both cases and controls) sampled at both clinics are analyzed at the Epicentre Research Laboratory through gold-standard methods for CNS infection diagnosis (microscopy, biochemistry, and culture) and a commercially available ME panel for multiplex PCR analyses of the cerebrospinal fluid. An additional blood sample from cases is collected on day 3 after admission. After initial clinical analyses in Mbarara, samples will be transported to Stockholm, Sweden for (1) validation analyses of a novel nucleic acid–based POC test, (2) biomarker research, and (3) serotyping and molecular characterization of *S. pneumoniae* and *N. meningitidis*.

**Results:**

A pilot study was performed from January to April 2019. The PI-POC trial enrollment of patients begun in April 2019 and will continue until September 2020, to include up to 300 cases and controls. Preliminary results from the PI-POC study are expected by the end of 2020.

**Conclusions:**

The findings from the PI-POC study can potentially facilitate rapid etiological diagnosis of CNS infections in low-resource settings and allow for novel methods for determination of the severity of CNS infection in such environment.

**Trial Registration:**

ClinicalTrials.gov NCT03900091; https://clinicaltrials.gov/ct2/show/NCT03900091

**International Registered Report Identifier (IRRID):**

DERR1-10.2196/21430

## Introduction

### Pediatric Central Nervous System Infections and Their Etiology

Infections of the central nervous system (CNS) are life-threatening conditions affecting thousands of children worldwide, resulting in significant morbidity and mortality, and contributing to the current burden of disease in low-income countries [1,2]. When correctly treated, mortality falls significantly. However, many survivors are often left with neurological sequelae [3-5]. In most African countries, the etiology of CNS infections among children is often unknown due to the lack of advanced laboratory tests [6,7]. Although CNS infections can be caused by different infective agents, such as bacteria, viruses, and parasites, the symptoms of the infection, such as fever, are similar [8,9]. The common symptoms of CNS infection make it difficult to distinguish between different causes of infection clinically, posing challenges to clinical fever case management. Globally, the most common pathogens causing bacterial CNS infections beyond the neonatal period are *Neisseria meningitidis, Streptococcus pneumoniae*, and *Haemophilus influenzae* type B (Hib) [10]. When managing bacterial infections, it is important and sometimes crucial that antibiotics, if available, are administered without delay [11]. At the same time, the irrational use of antibiotics for the treatment of nonbacterial infections is a global public health concern that leads to increased development of antibiotic resistance [12]. In order to minimize preventable deaths and severe outcomes in children, it is crucial to direct research toward better and robust diagnosis of CNS infections.

### Etiology of Childhood CNS Infections in Southwestern Uganda

Uganda is a low-income country with a high prevalence of malaria, HIV, and other infectious diseases. In the Mbarara district of Southwestern Uganda, a child presenting with fever at a health facility is typically suspected of having either malaria or an unidentified bacterial/viral infection. Such patients are routinely tested for malaria using antigen-based rapid diagnostic point-of-care (POC) tests, commonly known as malaria rapid diagnostic tests (RDTs); if the test result is positive, the patient is treated for malaria. However, if the test result is negative, then empiric antibiotics are often prescribed without confirmation of the bacterial cause of infection [12]. One of the major reasons for this routine is the lack of adequate diagnostic methods [13]. A study conducted in the Mbarara district in Uganda from 2009 to 2012 showed that the bacterial etiologies of childhood CNS infection to primarily be *S. pneumoniae*, nontyphoid Salmonella, and Hib [14]. Vaccination against Hib and *S. pneumoniae*, 2 major causative bacterial agents in childhood CNS infection, has been added to the child immunization program in Uganda in 2003 and 2013, respectively. As described elsewhere, immunization programs have changed etiologies of invasive infectious diseases, allowing for previously infrequent pathogens to rise and take leading roles in infection etiology [15]. Whether this epidemiological shift is also happening in Uganda is important to study.

### A Need for Novel Rapid Microbiological POC Tests Integrated Into the Laboratory

#### Development of POC tests for CNS infections

The current gold-standard laboratory methods to confirm suspected cases of CNS infection are bacterial culture and PCR analyses of cerebrospinal fluid (CSF) and blood [16]. However, a vast number of cases in sub-Saharan Africa occur in areas with little or no access to laboratory diagnostics, resulting in mistreatment and poor clinical outcomes [6]. To improve clinical management of patients with suspected CNS infections in resource-limited settings, new field-friendly, easy-to-use, low-cost, and reliable diagnostic POC assays are greatly needed. To maximize the POC benefit, we have previously shown that design and development of tests must be conducted with a focus on needs and capacities of intended end users [17].

#### Multi-POC for Bacterial Meningitis Developed for Resource-Limited Settings

We have currently developed protein-, immuno-, and DNA-based platforms amenable for the POC multiplex format [18,19]. The DNA technologies are paper based, using printed microarrays to capture specific DNA targets by vertical flow and displaying the results colorimetrically [20]. These methods make use of traditional PCR as well as recombinase polymerase amplification, a nucleic acid amplification technique which does not require thermal cycling. Recombinase polymerase amplification combines the advantage of sensitivity and short turnaround time for analyses, making it well suited for laboratories without capacity for performing advanced molecular-based assays [21]. Paper-based POC tools offer not only a superior advantage in terms of costs and simplicity of use, but also when it comes to logistics, as they are easy to transport, store, and ultimately dispose safely via incineration.

#### A Commercially Available Multiplex PCR Instrument for Meningitis/Encephalitis Diagnostics

Concurrently, a new PCR meningitis/encephalitis (ME) panel is being marketed as a multiplex and fast instrument for integrated analysis of CSF specimens [22]. An increasing number of clinics in high-income countries (HICs) are now implementing its use as it has shown good performance for the diagnosis of CNS infections [23]; however, no studies have so far, to our knowledge, evaluated its clinical performance, influence on patient management, or clinical usability for the diagnosis of pediatric CNS infections in low-income settings.

#### Novel Biomarkers for Future POCs

A promising biomarker related to viral infections is Myxovirus resistance protein A (MxA). MxA is an intracellular protein that is upregulated upon activation of the antiviral defense. Because of its potential to function as a biomarker for viral infective agents, MxA is possibly an important complement to current inflammatory biomarkers that mostly focus on bacterial infection [24-26]. The correlation between MxA and the presence of viral encephalitis has previously been reported; however, this is only through histological analyses of brain tissue samples [27].

The mapping of the proteomic characteristics of febrile children with varying clinical signs of severe disease using an established, highly multiplexed antibody suspension bead protein microarray platform (Luminex) will be carried out [28,29]. Multivariate and machine-learning methods can be employed for the extraction of protein expression profiles that robustly correlate or predict clinical patterns such as disease severity, hospitalization, organ failure, and other complications.

#### Molecular Mechanisms of Potential Virulence Traits

The pathogen *N. meningitidis* is known to cause rapid onset of severe sepsis and meningitis. Several virulence factors are well known but how the pathogen progresses from an asymptomatic colonizer to an invasive infection remains unclear. Previous research has identified a specific capsule RNA thermosensor that is able to sense environmental temperature [30]. This temperature-sensing mechanism enables the bacterium to increase capsule production to evade host complement-mediated killing [31]. Specific sequence polymorphisms of the RNA thermosensor have also been linked to invasive *N. meningitidis* isolates [32]. Identification and surveillance of these RNA elements within naturally occurring populations of *N. meningitis* could aid the further development of tailored diagnostics and treatment.

### Aim

The overarching aim of the Pediatric Infection-Point-of-Care (PI-POC) clinical trial is to strengthen the capacity for differential diagnosis and management of childhood CNS infections in low-income health systems.

The specific objectives of the trial are the following (Table 1):

• To evaluate the diagnostic accuracy of novel nucleic acid-based assays for etiological diagnosis of bacterial CNS infection.

• To evaluate clinical performance, influence on patient management, and clinical usability of a commercially available multiplex PCR-based ME panel in managing pediatric CNS infection in a low-income setting.

• To compare differences in the etiology of confirmed childhood CNS infection before and after the introduction of the pneumococcal conjugate vaccine.

• To study the putative biomarker MxA in plasma in cases with viral CNS infection in comparison with that in cases of nonviral CNS infection.

• To study the proteomic profile, in CSF and in plasma, of children with severe versus uncomplicated infections.

• To study the prevalence, serogroup distribution, and molecular characteristics of *N. meningitidis* virulence traits.

**Table 1 table1:** Summary of objectives, samples, and aims of the PI-POC^a^ study.

Objective	Aim	Specimen analyses	Specimen utilized
I	Validating a novel nucleic acid-based multi-POC^b^ method developed for the identification of CSF^c^ pathogens.	Sweden	CSF and cases
II	Evaluating the clinical utilization of a commercially available multiplex ME^d^ PCR panel in a low-income setting.	Uganda	CSF and cases
III	Updating current etiology of pediatric CNS^e^ infections in Mbarara and comparing it to the pre-pneumococcal conjugate vaccine era.	Uganda/Sweden	CSF and cases
IV	Validating MxA^f^ as a blood biomarker for differentiation of viral/nonviral cause of CNS infection.	Sweden	Plasma and cases and controls
V	Comparing proteomic characteristics of severe/nonsevere childhood infection and identification of novel biomarkers for severe pediatric infections.	Sweden	CSF, cases, plasma, and cases and controls
VI	Identifying mechanisms of virulence traits of *Neisseria meningitidis* isolated from pediatric patients.	Sweden	Nasopharyngeal swabs and cases and controls

^a^PI-POC: Pediatric Infection-Point-of-Care (trial).

^b^POC: point of care.

^c^CSF: cerebrospinal fluid.

^d^ME: meningitis/encephalitis.

^e^CNS: central nervous system.

^f^MxA: Myxovirus resistance protein A.

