#### Control Definition

Controls included children aged 0 months to 12 years with a fever and not meeting the case definition, seeking care at the outpatient departments of MRRH or HICH. For every case, 1 sex- and age-matched control is included. When age matching, we allow flexibility to match up to 1 month of age for newborns, within 6 months for infants, and within a year for children from 1 to 12 years. The control definition is chosen to cater for all stated objectives of the trial, without subjecting healthy children to unnecessary and often painful diagnostic procedures.

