#### Cerebrospinal Fluid (Cases Only)

CSF is collected through lumbar puncture (LP) by study clinicians at MRRH or HICH. LP is delayed or not performed in the presence of contraindications (signs of elevated intracranial pressure, focal neurological signs, local infection in the area of the puncture, signs of bleeding disorders, and cardiorespiratory compromise). The collected CSF is prioritized for patient care and routine primary laboratory diagnostics at the Epicentre Research Laboratory. Residual CSF is biobanked for further analyses.

To control for possible contamination, a sample of sterile water was poured into test tubes that are used for CSF collection. This was done at regular intervals during the trial, following the same procedure as when CSF is being collected from patients.

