**Controls**					
	Blood: Hematology, HIV serology (and confirmation), malaria RDT, biobank	1-2 mL	—	Routine clinical analyses (same day at the Epicentre Laboratory).	Proteomics analyses for profiling of biomarkers including MxA (later at the SciLifeLab).
	Nasopharyngeal swabs: Biobank	1 swab	—	—	Typing of bacteria and bacterial whole-genome sequencing (later at the Karolinska Institutet and SciLifeLab).

^a^Additional testing for clinical care, such as TB GeneXpert or TB ZN, was performed according to clinical needs and at the discretion of the medical officer.

^b^RDT: rapid diagnostic test

^c^CSF: cerebrospinal fluid.

^d^ME: meningitis/encephalitis.

^e^MxA: Myxovirus resistance protein A

^f^SciLifeLab: Science for Life Laboratory.

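### Objective V promises a severe-versus-uncomplicated proteomic comparison in CSF and plasma, but the only contrast the article defines (cases versus febrile outpatients) is unavailable in CSF and confounded in plasma.

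*Protocol article*

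**What the plan says.** The Aim section states Objective V as "To study the proteomic profile, in CSF and in plasma, of children with severe versus uncomplicated infections". Table 1 gives its aim as "Comparing proteomic characteristics of severe/nonsevere childhood infection and identification of novel biomarkers for severe pediatric infections" and its specimens as "CSF, cases, plasma, and cases and controls", which is most naturally read as CSF from cases and plasma from both groups.

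The abstract's objective paragraph describes the proteomic work differently: "proteomics profiling of blood from children with severe CNS infection as compared to outpatient controls with fever yet not severely ill". CSF is not mentioned there.

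The Statistical Methods and Data Analysis section plans to report protein differences between samples and controls. The Control Definition section says that "The control definition is chosen to cater for all stated objectives of the trial".

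On sampling, the article is consistent. The abstract, the CSF subsection of Biological Samples and Table 2 all restrict CSF to cases. For controls, Table 2 lists only a nasopharyngeal swab and "Blood: Hematology, HIV serology (and confirmation), malaria RDT, biobank".

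**The concern.** The objective names two severity groups and two specimens, so a reader expects severe and uncomplicated children to be compared in both CSF and plasma. The article identifies the less severe group only as the outpatient controls, who have no lumbar puncture. The contrast that it spells out therefore cannot be carried into CSF.

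The plasma half has a different difficulty. Cases enter on suspicion of CNS infection, and controls are outpatients who do not meet the case definition. A protein that differs between them may reflect severity, CNS involvement or the setting in which the child was recruited. What is at stake is the claim: a signature of suspected CNS infection could be published as a signature of severe childhood infection.

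**Working it through.** The article gives no sample size, effect size or power for Objective V, so there is no figure to reproduce. The check sets the passages side by side.

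**1. Which groups does the article name for the proteomic contrast?** The abstract treats CNS cases as severe and febrile outpatients as not severely ill. Study Site and Design describes controls in the same terms. The statistics section contrasts samples with controls. No passage names an uncomplicated group among the cases.

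**2. Which specimens exist in those groups?** The planned number of cases is about 300 (Study Size section), with one matched control per case (Control Definition), hence about 300 controls.

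| Specimen | Cases | Controls |
|---|---|---|
| CSF | up to about 300 | 0 |
| Plasma | up to about 300 | up to about 300 |

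The zero does not depend on how many controls are finally enrolled.

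**3. What does the plasma contrast estimate?** By design the groups fill only two of four cells:

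| | Treated as severe | Treated as not severe |
|---|---|---|
| Suspected CNS infection, emergency department or ward | all cases | none |
| No suspected CNS infection, outpatient | none | all controls |

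The case-control difference in a protein is thus: severity effect + CNS-presentation effect + setting effect. That is one observed difference for three unknowns. Matching on age and sex does not separate them, because none of the three is age or sex. There is no group with severe infection outside the CNS.

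Nor does case status measure severity well. Under the Case Definition, fever with photophobia qualifies, as does fever with a Glasgow score of 14 in a verbal child.

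**4. Is another severity comparison possible?** Yes, within cases. The section on novel biomarkers speaks of febrile children across a range of clinical severity and of relating proteins to organ failure and complications. The case criteria run from irritability to disturbed breathing. Study Variables records consciousness at enrolment, and length of stay and complications from the records.

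For scale only, the standardized mean difference detectable for one protein is

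SMD = (1.960 + 0.842) × √(1/n1 + 1/n2).

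This assumes a two-sided 0.05 level, 80% power and no multiplicity correction. The number with usable CSF (300 or 160) and the share severe are also assumptions, not figures from the article.

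| Cases with CSF | 10% severe | 25% severe | 50% severe |
|---|---|---|---|
| 300 | 30 vs 270: 0.54 | 75 vs 225: 0.37 | 150 vs 150: 0.32 |
| 160 | 16 vs 144: 0.74 | 40 vs 120: 0.51 | 80 vs 80: 0.44 |

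A within-case comparison could therefore be informative. Correction for many proteins would raise every entry.

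**5. Would CSF be equally available across severity?** Probably not. The CSF subsection delays or omits lumbar puncture with, among other things, signs of raised intracranial pressure, focal neurology or cardiorespiratory compromise, and it banks only what is left after routine diagnostics. Some of the sickest cases may give no CSF, so a within-case CSF comparison could be selectively truncated at its severe end.

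**The case against.** The strongest reply is that the article never promises a case-control comparison in CSF. The Objective V bullet does not mention controls, and Table 1 openly lists CSF for cases only. The background section signals a severity gradient, and the data for it are collected. The abstract may simply be condensed: it names blood where it names controls, which agrees with Table 1. The sentence that the control definition serves all objectives cannot mean that controls are the comparator everywhere, since Table 1 uses cases alone for Objectives I to III. A rule dividing cases by severity may sit in the full protocol or analysis plan, which an article need not reproduce.

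Much of this stands. A reader might infer that the CSF comparison has no second group at all and cannot be estimated. The documents do not support that: it would follow only if severe had to mean case and uncomplicated had to mean control, and a second group can be formed inside the cases. The absence of a within-case severity rule is likewise not held against the article.

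The reply does not remove two things. The contrast the article does state, in the abstract and the statistics section, is not the one that could serve CSF. And the plasma confounding follows from the recruitment rules as printed. The ethical reason for the choice of controls is sound and explains that limit, but does not widen what the contrast can show.

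**Conclusion.** The point holds in a limited form. The case-versus-outpatient contrast is the only one defined; it has 0 controls in CSF. In plasma, severity overlaps completely with suspected CNS presentation and care setting, so by itself it cannot support a claim about severe childhood infection in general. A severity analysis within cases is feasible in both specimens but is not the contrast stated. The abstract (blood), the Aim (CSF and plasma) and Table 1 (CSF from cases only) need to be brought into line.

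This rests on reading the abstract and the statistics section as the definition of the proteomic contrast. If the full protocol already specifies a within-case severity analysis, what remains is the wording and the limit on the plasma claim. The importance is moderate: Objective V is one of six in a study that calls itself exploratory, and no new sampling is needed.

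**What to change.** 1. Limit the case-control contrast to plasma and call it suspected CNS infection versus febrile outpatients.
2. State that the CSF part of Objective V is a within-case severity analysis using data already collected: coma score at inclusion, complications and length of stay. The Case Definition uses the Blantyre score for preverbal children and the Glasgow score for verbal ones, so the grading needs common categories. Report the number and share of cases with usable CSF at each severity level.
3. Run the same within-case gradient in plasma, and base any severity-biomarker claim on it rather than on the case-control difference.
4. Align the abstract's objective paragraph, the Objective V bullet and Table 1.

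Confirmed infection versus cases with normal CSF and negative tests may be added as a secondary contrast. It addresses etiology and does not answer the severity question.

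The cost is rewording and a small amount of extra analysis, with no further samples. The price is a narrower claim.
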